### 4.2. Analysis

Statistical analysis will be conducted using R software, version 4.2.1. or later. Norms for measurements of the larynx and trachea will be defined with the following percentiles: 5th, 10th, 25th, 50th (median), 75th, 90th and 95th. Additionally, density charts will be drafted to visualize the distribution of data for each measurement. Normality of distribution will be assessed using the Shapiro–Wilk test and based on visual assessment of histograms. Differences in each measurement between subgroups (sex, Apgar score, delivery method) will be verified using t-test and ANOVA or their non-parametric equivalents, as appropriate. Correlation analysis will be conducted between measurements of the larynx and trachea and gestational age, age at the time of the study, Apgar score at the 1st, 5th and 10th minutes of life, gender, type of delivery, birth weight and length, and weight on the day of the examination. Additionally, regression analysis (univariate and multivariate) will be used to determine the relationship between the above anthropometric measurements and measurements of the larynx and trachea.

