## Abstract

Diseases of the larynx and trachea are a heterogenous group of disorders. Their diagnosis frequently requires invasive methods. Ultrasound is a non-invasive, repeatable and safe diagnostic method, which has recently, thanks to the development of technology, provided for very accurate imaging of even small structures, as well as their assessment on dynamic examination. Ultrasound examination of the larynx and trachea will be performed in 2022–2023 in a group of randomly selected 300 stable neonates born between 32 and 42 weeks of gestation. The results of this study will be presented after data collection in accordance with the adopted methodology. To date, this will be the first study to describe the ultrasound anatomy of the larynx and trachea and to establish reference ranges for the size of individual structures of the larynx and trachea in the neonatal population. We expect that our study will contribute to the further development of this part of ultrasonography and will reduce the number of invasive procedures performed in the diagnostics of these organs in the future. This manuscript is a study protocol registered at ClinicalTrials.gov (Identifier NCT05636410) and approved by the Bioethics Committee of the Medical University of Warsaw (KB 65/A2022).

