## 3. Materials and Equipment

Ultrasound examination of larynx and trachea will be performed in the Department of Neonatology and Neonatal Intensive Care at the Medical University of Warsaw and the Department of Neonatology at Ujastek Medical Center in Cracow, in 2022–2023, in a group of three-hundred randomly selected neonates, born between 32 and 42 weeks of gestation, who are stable and do not require intubation. The examination will take place in a specially prepared ultrasound room; therefore, only stable newborns who do not require intubation will be included. Prior to that, written consent will be obtained from at least one parent prior to the examination.

Inclusion criteria:Gestational age ≥32 weeks.

Exclusion criteria:Gestational age <32 weeks;Presence of significant congenital anomalies;Intubated neonate;Unstable neonate.

As recommended by WHO for similar research projects, a representative study group should include at least 200 study participants [14]. To improve the quality and reliability of the results, the number of participants for this study was set at 300. The calculated inter-observer and intra-observer concurrence (Kappa coefficient) will be calculated for all measurements.

The examination will be performed with high-class ultrasound machine (Philips Epiq 97G device, using the eL18-4 linear probe), using water-based, hypoallergic ultrasound gel (Aquasonic 100, Parker laboratories Inc., Fairfield, CT, USA), previously warmed to body temperature.

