## 5. Expected Results

The main aim of the study is the accurate description of the ultrasound anatomy of the larynx and trachea, as well as the establishment of an examination standard for these organs in neonatal populations. The next objective is to set reference ranges for the size of individual structures of the larynx and trachea with respect to newborns. The study also aims to develop a universal method of ultrasound assessment of the mobility of the vocal cords on dynamic examination and to determine a rule for predicting the expected size of the laryngeal and tracheal structures in relation to anthropometric measurements.

Another purpose of the study is to promote the use of a non-invasive examination, such as ultrasonography, in the diagnosis of diseases of the larynx and trachea with respect to the youngest patients. Additionally, the study will be conducted to develop artificial intelligence algorithms based on artificial neural networks, which will allow one to make larynx and trachea diagnostics easier in the future.

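### The norms are defined as percentiles with no conditioning on gestational age or body size, so their limits will be off at both ends of 32 to 42 weeks for any measurement that grows with maturity

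*Protocol article*

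**What the plan says.** Section 4.2 (Analysis) defines the product: "Norms for measurements of the larynx and trachea will be defined with the following percentiles", seven in all from the 5th to the 95th, with the median among them. Nothing in that sentence or around it makes the percentiles depend on gestational age, weight or length.

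The population is "300 stable neonates born between 32 and 42 weeks of gestation" (Abstract; section 3 gives the same span).

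The other planned analyses are separate from the norms:
- **Subgroup tests.** "Differences in each measurement between subgroups (sex, Apgar score, delivery method) will be verified using t-test and ANOVA". Gestational age is not among these subgroups.
- **Correlations.** Each measurement is correlated with gestational age, age at study, birth weight and length, examination-day weight and other items.
- **Regression.** Univariate and multivariate regression is listed as an additional analysis, with no stated role in setting the limits.

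Section 5 (Expected Results) names reference ranges as an objective and, separately, aims "to determine a rule for predicting the expected size of the laryngeal and tracheal structures in relation to anthropometric measurements".

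**The concern.** A percentile taken over the whole 32-42-week span has 5% of the whole sample below it. It has 5% below it at each maturity only if the measurement does not vary with maturity. The protocol's own aim of predicting size from anthropometry presupposes that at least some structures do vary. For those, a low value mixes being small because immature with being small for one's maturity.

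The reference limits are what a clinician would take from this study, and section 6 hopes the work will reduce invasive procedures. At the lower limit, healthy preterm infants would be called small too often and term infants with abnormally small structures too seldom. At the upper limit the pattern reverses. Section 3 states no quota or strata for gestational age, so the limits would also depend on how many preterm infants happened to be enrolled.

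**Working it through.** **The plan's own figure.** The article gives no coverage or precision figure for the percentiles. Its only number is the sample size: "a representative study group should include at least 200 study participants", after which "the number of participants for this study was set at 300". That is a cited minimum rounded up, so there is no formula to reproduce.

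**Inputs from the article.** Weeks 32 to 42; n = 300; lower and upper limits at the 5th and 95th percentiles.

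**Assumptions (not in the article).** Standardised measurement y = b(GA − μ) + e, with e normal with SD √(1 − r²), and b = r / SD(GA). Correlation r from 0 to 0.7. Three mixes over whole weeks 32-42:
- A: uniform (mean 37.0, SD 3.16, 45% under 37 weeks)
- B: normal(37, 2.5), truncated (mean 37.0, SD 2.29, 42% under 37 weeks)
- C: normal(39, 1.8), truncated (mean 38.89, SD 1.69, 8% under 37 weeks)

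**Formula.** The pooled limit q5 solves Σ p(g)·Φ[(q5 − b(g − μ))/√(1 − r²)] = 0.05. The share of healthy infants of week g below it is Φ[(q5 − b(g − μ))/√(1 − r²)].

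**Worked cases, r = 0.5 (√(1 − r²) = 0.866).**
- Mix A, 33 weeks: b = 0.5/3.16 = 0.158, q5 = −1.645; (−1.645 + 0.158 × 4)/0.866 = −1.17; Φ = 12%.
- Mix C, 33 weeks: b = 0.5/1.69 = 0.2965, q5 = −1.654; (−1.654 + 0.2965 × 5.89)/0.866 = 0.11; Φ = 54%.
- Mix C, 40 weeks: (−1.654 − 0.2965 × 1.11)/0.866 = −2.29; Φ = 1.1%.

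**Healthy 32-34-week infants below the pooled 5th percentile (nominal 5%).**

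| r | Mix A | Mix B | Mix C |
|---|---|---|---|
| 0 | 5% | 5% | 5% |
| 0.1 | 6% | 7% | 9% |
| 0.3 | 9% | 11% | 22% |
| 0.5 | 12% | 16.5% | 43% |
| 0.7 | 15% | 23% | 73% |

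For all infants under 37 weeks the shares are milder: 6-7% at r = 0.1, 8-14% at r = 0.3, 10-22% at r = 0.5 and 11-34% at r = 0.7.

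**Term end, lower limit.** At 40 weeks, 1.6-2.7% (r = 0.3) or 0.4-1.1% (r = 0.5) lie below the pooled 5th percentile. Dividing by 5%, only 33-53% or 8-22% of the 40-week infants below their own-age 5th centile would be flagged.

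**Upper limit, r = 0.5.** Above the pooled 95th percentile: at most 0.4% at 33 weeks, and 12-19% at 41 weeks.

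**Dependence on case mix.** Holding r fixed across mixes changes the implied slope, so the columns do not show one measurement moved between mixes. For that, hold the slope fixed. Mix A at r = 0.5 has slope 0.158/0.866 = 0.183 residual SD per week. In mix C this gives 0.183 × 1.69 = 0.309, so r = 0.309/√(1 + 0.309²) = 0.295, close to the r = 0.3 row. The same measurement would thus put 12% of healthy 32-34-week infants below the limit in mix A and about 22% in mix C.

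**Would raw percentiles by week do instead?** 300/11 is about 27 infants per week, of whom 27 × 0.05 = 1.4 fall below the 5th percentile. SE = √(0.05 × 0.95/27.3)/0.103 = 0.40 SD, against √(0.05 × 0.95/300)/0.103 = 0.12 SD for all 300. Week-by-week percentiles are not workable; a model across all infants is.

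**The case against.** The strongest reply is that section 4.2 only lists which percentiles will be reported. It does not use the words raw or pooled, and does not exclude centiles by gestational age. This is a condensed article, and the method of centile estimation is often left to an analysis plan. Correlations with gestational age and size, regression, and a size-prediction rule are all planned, and a regression with a residual SD can yield centiles directly.

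Part of this stands. That the norms are a single unconditional set is an inference from the absence of any conditioning, not a statement in the text. It would also be too strong to say that the planned regression cannot give centiles. But the article does not leave the definition open: it says what the norms are, names the subgroups without gestational age, and gives the regression a separate purpose. The gap is the missing link between the two.

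The reply also limits the size. A reader might infer that a large share of preterm infants will be misflagged whatever the measurement. The documents do not support that: they give no correlation and no gestational-age mix, and section 4.1 includes angles and the amplitude and duration of vocal cord movement, which may not follow maturity at all. The largest shares arise in the term-heavy mix, where 32-34 weeks is about 2 of 300 infants (0.58% × 300 = 1.7).

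**Conclusion.** The point holds. As written, the norms are not conditional on gestational age or size, and nothing else in the plan feeds into the limits. For any measurement that rises with maturity, the direction of the error follows at both limits. Its size rests on the linear-normal model and on the assumed correlations and mixes: negligible to slight at r of 0.1 or less, and material from about r = 0.3.

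Two stronger readings are not supported:
- **That pooled limits would pass clearly abnormal term infants as normal in general.** A 40-week infant at its own 1st centile sits at the pooled 2.2nd to 3.4th percentile at r = 0.3, and so is still flagged. At r = 0.5 it sits at the 4.7th to 8.7th, which straddles the limit.
- **That preterm infants would be scanned weeks after birth.** The article sets no limit on age at scan, but it calls the subjects neonates and both collects and analyses age at study. A long delay is speculation.

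**What to change.** In section 4.2, define the 5th to 95th percentiles of each measurement as centiles from a model fitted to all measured infants. Condition on postmenstrual age at examination (gestational age plus age at study) and/or examination-day weight. Quantile regression, LMS/GAMLSS, or a mean-and-SD regression would each serve. Give 95% confidence intervals for the 5th and 95th centile curves. Keep the pooled percentiles as description, or as the norm for measurements where no dependence on maturity or size is found.

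Cost: a change of analysis wording. The covariates are already collected (section 4.1) and R is already the named software; no extra infants or examinations are needed. The drawbacks are charts or equations in place of one table, dependence on the chosen model, and wide intervals, or near-extrapolation, at the preterm end if few such infants are enrolled. The number of infants by gestational week should be reported beside the curves so that users can see where the limits are weak.

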## 5. Expected Results

The main aim of the study is the accurate description of the ultrasound anatomy of the larynx and trachea, as well as the establishment of an examination standard for these organs in neonatal populations. The next objective is to set reference ranges for the size of individual structures of the larynx and trachea with respect to newborns. The study also aims to develop a universal method of ultrasound assessment of the mobility of the vocal cords on dynamic examination and to determine a rule for predicting the expected size of the laryngeal and tracheal structures in relation to anthropometric measurements.

Another purpose of the study is to promote the use of a non-invasive examination, such as ultrasonography, in the diagnosis of diseases of the larynx and trachea with respect to the youngest patients. Additionally, the study will be conducted to develop artificial intelligence algorithms based on artificial neural networks, which will allow one to make larynx and trachea diagnostics easier in the future.

## 6. Discussion

This study will be effected subject to the following limitations. The first is the restriction of the research group to the Polish population. In order to increase the research group and increase its heterogeneity, recruitment of patients will take place in two Polish neonatal centers. The second limitation is the lack of a valid ultrasound examination standard and reference size standards for the larynx and trachea in the study population, so the obtained images and measurements may differ significantly between individual researchers. To reduce this problem, each researcher will be trained in the technique of obtaining the required images before the study begins. Furthermore, each researcher will be instructed in identification and measurement of individual trachea and larynx structures. Additionally, high-class ultrasound machines will be used to acquire the highest quality images.

To avoid bias, the ultrasound will be performed in the presence of one researcher, who will then measure the individual structures of the larynx and trachea. The other researcher’s measurements will take place independently with no information about patient history and without any contact between the researchers.

To date, no detailed description of the ultrasound anatomy of the larynx and trachea in the newborn population has been published considering the norms of the measurements of individual structures of these organs. We hope that our study will contribute to the further development of this part of ultrasonography and will reduce the number of invasive procedures performed on newborns in the future.

## Figures and Tables

**Figure 1 diagnostics-13-01578-f001:**
[figure not shown]
Study design diagram.

## Data Availability

This manuscript is a study protocol. No new data was created or analyzed in this study. Data sharing is not applicable to this article.
